## Abstract

**Background:**

Frailty resulting from the loss of muscle quality can potentially be delayed through early detection and physical exercise interventions. There is a demand for cost-effective tools for the objective evaluation of muscle quality, in both cross-sectional and longitudinal assessments. Literature suggests that quantitative analysis of ultrasound data captures morphometric, compositional, and microstructural muscle properties, while biological assays derived from blood samples are associated with functional information.

**Objective:**

This study aims to assess multiparametric combinations of ultrasound and blood-based biomarkers to offer a cross-sectional evaluation of the patient frailty phenotype and to track changes in muscle quality associated with supervised exercise programs.

**Methods:**

This prospective observational multicenter study will include patients aged 70 years and older who are capable of providing informed consent. We aim to recruit 100 patients from hospital environments and 100 from primary care facilities. Each patient will undergo at least two examinations (baseline and follow-up), totaling a minimum of 400 examinations. In hospital environments, 50 patients will be measured before/after a 16-week individualized and supervised exercise program, while another 50 patients will be followed up after the same period without intervention. Primary care patients will undergo a 1-year follow-up evaluation. The primary objective is to compare cross-sectional evaluations of physical performance, functional capacity, body composition, and derived scales of sarcopenia and frailty with biomarker combinations obtained from muscle ultrasound and blood-based assays. We will analyze ultrasound raw data obtained with a point-of-care device, along with a set of biomarkers previously associated with frailty, using quantitative real-time polymerase chain reaction and enzyme-linked immunosorbent assay. Additionally, we will examine the sensitivity of these biomarkers to detect short-term muscle quality changes and functional improvement after a supervised exercise intervention compared with usual care.

**Results:**

At the time of manuscript submission, the enrollment of volunteers is ongoing. Recruitment started on March 1, 2022, and ends on June 30, 2024.

**Conclusions:**

The outlined study protocol will integrate portable technologies, using quantitative muscle ultrasound and blood biomarkers, to facilitate an objective cross-sectional assessment of muscle quality in both hospital and primary care settings. The primary objective is to generate data that can be used to explore associations between biomarker combinations and the cross-sectional clinical assessment of frailty and sarcopenia. Additionally, the study aims to investigate musculoskeletal changes following multicomponent physical exercise programs.

**Trial Registration:**

ClinicalTrials.gov NCT05294757; https://clinicaltrials.gov/ct2/show/NCT05294757

**International Registered Report Identifier (IRRID):**

DERR1-10.2196/50325

## Introduction

Aging is associated with a gradual decline in muscle mass and function, contributing to an increased incidence and prevalence of chronic diseases [1,2]. This, in turn, often leads to situations of multimorbidity [3] and adversely affects functional autonomy [4]. The most severe manifestation of this condition is frailty, described as “a progressive decline in physiological systems that leads to decreased reserves of intrinsic capacity. This confers extreme vulnerability to stressors and increases the risk of various adverse health outcomes” [5]. Frailty is linked to dependency, hospitalization, institutionalization, falls, poor quality of life, and mortality [6-10], along with elevated health care costs [11,12]. While standardized diagnostic criteria are not universally established, the 2 most widely accepted ones [13,14] are rooted in the phenotype construct [4]. According to this construct, frailty is diagnosed when 3 or more of the following criteria are met: unintentional weight loss, self-reported exhaustion, reduced grip strength, slow gait speed, and low levels of physical activity. Moreover, the Cumulative Deficit Model—Frailty Index encompasses cognitive, functional, emotional, and nutritional status [15,16].

The frailty phenotype, as outlined by Fried et al [4], centers around muscle dysfunction [17]. Considering that weakness, slowness, and impairment of the muscular system are characteristic features of frailty, sarcopenia is likely a crucial physiopathological contributor [13,18]. Sarcopenia is a progressive skeletal muscle disease, and its prevalence tends to increase with age. Estimates suggest that sarcopenia affects between 6% and 19% of the general population aged 60 years and older, with variations depending on the applied definition [19]. Currently, the most widely used definitions come from the European Working Group on Sarcopenia in Older People 2 (EWGSOP-2) [20], the Definition and Outcomes Consortium (DOCS) [21], and the National Institute of Health Foundation (NIHF) [22]. According to the EWGSOP-2, reduced muscle strength serves as the initial criterion for probable sarcopenia, and the diagnosis is confirmed by reduced muscle mass and quality. Furthermore, when low physical performance is identified, sarcopenia is categorized as severe [20]. The DOCS supports the inclusion of both weakness (defined by low grip strength) and slowness (defined by low usual gait speed) in the definition of sarcopenia [21]. The NIHF defines sarcopenia as a loss of strength diagnosed by low grip strength, accompanied by low muscle mass [22].

In clinical care, the assessment of muscle mass and quality involves a semiquantitative evaluation using 2D images through dual-energy X-ray absorptiometry (DXA) and a body composition estimate through bioelectrical impedance analysis (BIA) [20]. It is worth noting that these techniques can be influenced by other variables, such as skeletal mass and a high BMI [23]. Radiological imaging enables comprehensive 3D mapping of muscle composition and microstructure. The proposed methods are magnetic resonance imaging (MRI) and computed tomography (CT) sequences, allowing the assessment of adipose fraction and fibrous microstructure, among other parameters [24-26]. However, because of their high cost and the potential for patient complications, these imaging methods are presently limited to research applications or as supplementary examinations for different primary indications [27].

Sarcopenia and frailty, although connected and associated with aging, are distinct conditions. Sarcopenia primarily centers around the musculoskeletal system, while frailty is a more multifactorial condition [28,29]. Various studies indicate that the prevalence of sarcopenia among older adults with frailty is higher than the prevalence of frailty among those with sarcopenia [28,30-32]. Adverse outcomes linked to muscular decline can be mitigated, delayed, or even reversed through early detection and interventions, including nutritional support and physical exercise programs [13,18,33]. Nonetheless, there exists a need for straightforward and dependable tools that facilitate the assessment of muscle quality and its implications for frailty [28,34].

Ultrasound, as a fast, noninvasive, and cost-effective imaging modality, is gaining rapid prominence for musculoskeletal examination [35,36]. Currently, clinical ultrasound images (B-mode) enable the assessment of muscle mass and morphology, encompassing measures such as muscle thickness, pennation angle, cross-sectional area, echo intensity, and fascicle length [37-39]. Despite ongoing efforts for standardization, these measurements remain highly reliant on the expertise and skills of the operator, and they do not provide definitive results for the early staging of muscle quality loss [37,40]. Ultrasound morphometric measurements of sarcopenia in older adults have demonstrated mild to moderate associations with frailty [41]. More recently, various quantitative ultrasound techniques have surfaced, involving the analysis of echogenicity, texture parameters, elastography, and acoustic wave properties. However, their translation to clinical practice is still limited [42-51]. Artificial intelligence is presenting new opportunities to objectify musculoskeletal ultrasound, with recent studies showcasing automatic muscle segmentation, fiber angle detection, and textural discrimination of muscle microstructures [52-55].

Biological biomarkers serve as valuable tools in diagnosing and stratifying patients, as well as in comprehending the underlying pathophysiology of diseases. Oxidative stress, a proinflammatory state, and immune aging play significant roles in the connection between nonspecific biomarkers and specific biological systems related to frailty and sarcopenia [56-59]. Recent studies have delved into the intricate interrelationships among various systems that underlie frailty through multi-omics approaches [60]. As an example, the FRAILOMIC initiative used blood samples to delineate a collection of biological biomarkers, encompassing both protective and risk factors. Notably, oxidative stress, vitamin D, and the cardiovascular system were found to be associated with frailty [61]. Despite these advancements, the currently available biomarkers exhibit weak individual associations with the clinical outcomes of sarcopenia and frailty. Furthermore, their ability to detect changes after physical intervention remains largely unknown.

A limited number of studies have explored the combination of ultrasound and blood-based biomarkers. In one study, changes in circulating biomarkers corresponding to a short-term resistance exercise intervention in older adults were identified. These changes were found to be significantly related to ultrasound leg cross-sectional area [62]. Associations were discovered between combined genetic and methylation scores and ultrasound-derived skeletal muscle morphometry in older women [63]. In another cross-sectional study, ultrasound characteristics of the quadriceps femoris in patients with sarcopenia were correlated with blood and urinary biomarkers [64].

In summary, there is a lack of simple and objective screening tools for diagnosing frailty and sarcopenia [28,34]. While clinical standardization of B-mode images is essential, there is also a requirement for advancements in ultrasound technology to develop quantitative indicators for assessing muscle quality [65,66]. This study is designed to assess objective methods for evaluating muscle quality using quantitative analysis techniques based on the analysis of ultrasound raw data combined with blood-based biomarkers. Additionally, the study aims to investigate the capability of these biomarkers to detect changes in muscle quality resulting from a physical exercise intervention program in older individuals with frailty.

The primary aim of this study is to assess the feasibility of combining point-of-care quantitative ultrasound parameters with blood-based assays for evaluating muscle quality and frailty in older adults. This evaluation will encompass both hospital settings and community care, with a focus on comparing the findings with traditional clinical evaluations.

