### Outcomes

#### Primary Outcomes

Investigating the association between quantitative ultrasound biomarkers related to muscle mass and quality (thickness [mm], cross-sectional area [cm^2^], perimeter [mm], pennation angle [degrees]) extracted from raw data and blood-based biomarkers, as well as their combinations with clinical variables. These clinical variables encompass frailty (FRAIL [short 5-question assessment of Fatigue, Resistance, Aerobic capacity, Illnesses, and Loss of weight] scale ranging from 0 to 5, with 0 indicating robustness and 5 indicating frailty, and Frailty phenotype by Fried et al [4], ranging from 0 [robust] to 5 [frail]), sarcopenia (SARC-F [Strength, Assistance with walking, Rising from a chair, Climbing stairs, and Falls] scale scores ranging from 0 [robust] to 10 [sarcopenic]), physical function (Short Physical Performance Battery [SPPB] Scale score ranging from 0 to 12, where 0 indicates the lowest physical performance and 12 indicates the highest performance), International Physical Activity Questionnaire scores ranging from 0 (lowest) to 3 (highest), Gait Speed Test in seconds, grip strength measured by Jamar dynamometer in kilogram, disability (Global Deterioration Scale, consisting of 7 stages), Barthel Index (ranging from 0 [total dependent] to 100 [independent]), Lawton and Brody Index (scores from 0 [dependent] to 8 [independent]), nutritional status (Mini Nutritional Assessment—Short Form), body composition (DXA), and quality of life (EQ-5D-5L) within 3 cohorts of older adults: hospital control cohort, hospital exercise cohort, and primary care cohort.

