### Statistical Analysis

The study population will be characterized based on demographic and clinical attributes. Categorical data will be summarized with frequency and percentage representations. Continuous data will be described using mean, SD, median, and the 25th and 75th percentiles. Furthermore, the distribution of ultrasound parameters with respect to the primary endpoint will be depicted using graphical techniques. The correlation of quantitative biomarkers will be evaluated for each multifactorial clinical evaluation parameter using the Pearson correlation coefficient for continuous variables and the Spearman correlation coefficient for categorical variables [88]. Unpaired tests, such as the Student *t* test, will be used for comparing means of biomarkers among various acquired patient cohorts and for stratified patient subgroups based on the frailty scales outlined in Textbox 1. To manage the extensive array of ultrasound and blood biomarkers, a robust statistical analysis plan will be implemented. This plan will incorporate correction methods to address the risk of type I errors associated with multiple comparisons. Specifically, for the primary outcome concerning biomarker-clinical associations, we will use Lasso regression. This technique automates the selection of relevant variables, reducing the necessity for extensive corrections and improving interpretability. Paired statistics will be applied in the statistical analysis for longitudinal monitoring, encompassing both interventions and clinical follow-up. The monitoring period in hospital and primary care environments will differ to accommodate the distinct follow-up workflows in each setting. The duration of primary care follow-up aligns with established norms [89,90]. To account for differences in follow-up duration among cohorts over time, our data analysis will incorporate appropriate statistical methods, potentially enabling adjustments for these variations. For the secondary objective, the impact of physical intervention in 50 patients will be compared with 50 patients with no intervention. With 80% power, the planned population size will enable the detection of a biomarker with a medium effect size of E/S=0.284 at a 2-sided α level of .05.

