The analysis revealed significant moderate correlations between muscle cross-section and thickness and DXA parameters (Table 3). Notably, the highest correlation (*r*=0.539, *P*<.001) was observed between DXA appendicular mass and muscle cross section. Additionally, significant weak correlations were identified between functional variables (such as gait speed, grip strength, and SPPB) and ultrasound morphometric parameters (including muscle section, thickness, and pennation angle; indicated in Table 3 in rows 7, 8, and 9, respectively). The frailty scale (FRAIL, Fried et al [4]) and the sarcopenia scale (SARC-F) exhibited weak but significant associations with muscle cross section as illustrated in row 2 of Table 3. Additionally, significant weak correlations were identified between pennation angle and measures of independence (Barthel and Lawton Index) as well as nutritional assessment (Mini Nutritional Assessment—Short Form) as detailed in Table 3. Notably, age did not demonstrate a significant association with ultrasound morphometric variables (*r*=–0.023, *P*=.82; *r*=0.002, *P*=.98; and *r*=–0.072, *P*=.47, respectively). However, a weak correlation was observed between BMI and muscle thickness.

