### Comparison With Prior Work

Recent literature indicates that impaired mobility associated with aging is not solely attributed to changes in skeletal muscle mass; other factors contributing to muscle quality also play a crucial role. Notably, alterations in muscle tissue composition, characterized by elevated levels of intramuscular adipose tissue and intramyocellular lipids, have been identified as factors that negatively impact muscle functional capacity [17,65,93]. Our hypothesis suggests that quantitative ultrasound biomarkers derived from raw data may exhibit superior discriminative performance, greater reproducibility, and enhanced ease of use compared with the current state-of-the-art assessments based on B-mode images. B-mode morphological ultrasound parameters are primarily linked to muscle mass and demonstrate limited sensitivity in the diagnosis of sarcopenia. Quantitative ultrasound biomarkers derived from raw data have consistently demonstrated their ability to capture both tissue composition and microstructural properties. Furthermore, they have exhibited a greater capacity to encode richer information content compared with ultrasound B-mode images in artificial intelligence models, as highlighted in prior research [52,54,83,84]. Ultrasound spectroscopy parameters and tissue acoustic properties, such as speed of sound and attenuation, have been associated with tissue composition [47] and viscoelastic changes in muscle [49] among older individuals with sarcopenia. Specifically, speed of sound has demonstrated correlations with MRI adiposity estimates in the calf muscles [94], CT assessment of the psoas muscle [95], and short-term changes in muscle due to immobilization [96]. The ultrasound statistical analysis of the envelope signal in soft tissues has been correlated with the concentration, spacing, and directionality of microstructural scatterers [78]. Additionally, texture features derived from radiomics analysis capture musculoskeletal composition and microstructure. This approach has been successfully applied to differentiate various musculoskeletal conditions, including muscle spasticity, dynapenia, myositis, fibromyalgia, Duchenne muscular dystrophy, and exercise-induced muscle damage [55,97]. Being acquired at the early stages of ultrasound image formation, ultrasound raw data may play a crucial role in minimizing equipment- and operator-dependent bias. Additionally, they have the potential to provide data-based guidance for examiners with limited sonographic acquisition expertise.

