### Limitations

The study does have certain limitations, notably the absence of access to a gold standard for muscle quality assessment. Established radiological techniques such as CT and MRI serve as references for muscle composition and microstructure but come with patient complications and are not widely accessible in the clinical environments under investigation. Instead, we rely on a multifactorial clinical assessment, patient stratification, and carefully controlled interventions to evaluate changes in muscle quality. The exploration of ultrasound technology is limited to backscattering ultrasound data derived from beamformed raw data. Other ultrasound quantitative technologies, such as shear wave elastography [43] and blood flow measurements based on Doppler sequences [99], are excluded from the scope because of their lack of routine availability in point-of-care ultrasound devices and the added complexity they introduce to the protocol execution. The disparate monitoring periods in hospital (16 weeks) and primary care environments (1 year) are designed to accommodate the distinct follow-up workflows in both settings. We also acknowledge that the randomization of populations in the secondary goal is conducted on an institutional basis, which could introduce statistical bias if the populations in the 2 institutions differ. To address this potential bias, we will perform a *post hoc* analysis to examine the characteristics of the populations in the various recruitment centers. The dimensioning of the primary care follow-up aligns with periods established in previous studies for the general population [89,90].

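### The study aims at muscle quality as distinct from mass, but no listed reference variable measures quality and no planned analysis names muscle mass as a conditioning variable, so the two cannot be told apart

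*Protocol article*

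**What the plan says.** **The target.** The Introduction says "This study is designed to assess objective methods for evaluating muscle quality using quantitative analysis techniques" and gives the primary aim as the feasibility of combining ultrasound and blood assays "for evaluating muscle quality and frailty in older adults". The Abstract's objective adds the longitudinal side: "to track changes in muscle quality associated with supervised exercise programs".

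**Mass against quality.** Comparison With Prior Work says mass alone does not explain impaired mobility and points to muscle composition as well. It also says: "B-mode morphological ultrasound parameters are primarily linked to muscle mass and demonstrate limited sensitivity in the diagnosis of sarcopenia". It then hypothesises that markers from raw data will discriminate better than B-mode measures. Primary Outcomes, however, names only morphometric ultrasound measures and labels them as "quantitative ultrasound biomarkers related to muscle mass and quality (thickness [mm], cross-sectional area [cm^2^], perimeter [mm], pennation angle [degrees" (the list ends there).

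**The reference variables.** Primary Outcomes and Textbox 2 list frailty and sarcopenia scales, SPPB, gait speed, grip strength, activity, disability, nutrition, quality of life and DXA. The DXA outputs are total muscle mass, ALM, ALM/h², total fat and fat percentage. Limitations concedes "notably the absence of access to a gold standard for muscle quality assessment" and relies instead on the clinical assessment, stratification and the intervention.

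**The analysis.** Statistical Analysis plans: "The correlation of quantitative biomarkers will be evaluated for each multifactorial clinical evaluation parameter using the Pearson correlation coefficient for continuous variables", with Spearman for categorical variables and Lasso for the primary outcome. It also plans regression models for the influence of covariates, which it does not name. DXA mass appears only as one more variable to be correlated with.

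**The concern.** If a biomarker tracks lean mass, and lean mass is related to strength and performance, the biomarker will correlate with grip, SPPB and gait speed even if it carries nothing about the quality of the muscle. A correlation taken separately with each clinical variable gives the same kind of result for a quality marker and for a mass marker.

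What is at stake is the study's own hypothesis. The Discussion expects the advanced models to correlate better with baseline characteristics than the morphometric measures do. In Table 3 the largest correlations are those of thickness and area with DXA mass (0.440 to 0.539), so a model can improve on that table by reproducing lean mass more closely. Information beyond mass, which is what the raw-data approach is meant to add, is not isolated by any analysis the article describes.

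**Working it through.** The plan states no figure on this point, so there is none to reproduce. The check illustrates how much of a printed correlation mass could account for.

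**Inputs**
- Table 3: area-ALM r = 0.539 (in the Results text, the highest correlation "was observed between DXA appendicular mass and muscle cross section"); area-grip r = 0.372; thickness-ALM r = 0.440; thickness-grip r = 0.240.
- Grip-ALM correlation, called m: not in the document. Assumed range 0.3 to 0.7.
- Evaluable sample: 200 × 0.9 = 180, from the 10% exclusion allowed under Sample Size.

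**Step 1. Correlation with grip after adjustment for ALM**

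Partial r = (r_xy − r_xm × m) / √[(1 − r_xm²)(1 − m²)]

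For area at m = 0.5: (0.372 − 0.539 × 0.5) / √[(1 − 0.2905)(1 − 0.25)] = 0.1025 / 0.7295 = 0.14.

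| m (assumed) | area-grip, adjusted (raw 0.372) | thickness-grip, adjusted (raw 0.240) |
|---|---|---|
| 0.3 | 0.26 | 0.13 |
| 0.4 | 0.20 | 0.08 |
| 0.5 | 0.14 | 0.03 |
| 0.6 | 0.07 | -0.03 |
| 0.7 | -0.01 | -0.11 |

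The adjusted value reaches zero at m = 0.372/0.539 = 0.69 for area and at m = 0.240/0.440 = 0.545 for thickness.

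**Step 2. A marker that carries mass only**

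Take a marker with r = 0.539 to ALM and no other link to grip. Its raw correlation with grip is 0.539 × m. By Fisher's z, power at n = 180 (two-sided 0.05) is approximately Φ(atanh(r) × √177 − 1.96). For m = 0.5: r = 0.27, atanh(r) = 0.276, 0.276 × 13.30 − 1.96 = 1.72, power 96%.

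| m (assumed) | raw r with grip | chance of P<.05 at n = 180 |
|---|---|---|
| 0.3 | 0.16 | 58% |
| 0.4 | 0.22 | 83% |
| 0.5 | 0.27 | 96% |
| 0.6 | 0.32 | 99% |
| 0.7 | 0.38 | 100% |

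Such a marker has no quality content by construction, so the table shows only that a significant raw correlation is no evidence of quality. It says nothing about what this study's markers contain.

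**Step 3. How far Table 3 can be trusted as input**

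With t = r√[(n − 2)/(1 − r²)], the printed P values can be set against n = 66.
- Thickness-BMI: r = 0.269 gives P = .029 at n = 66. The printed .009 needs n of about 93.
- Thickness-grip: r = 0.240 gives P = .052 at n = 66. The printed .02 (rounded) fits n of 88 to 102.
- Thickness-DXA total fat: r = 0.271 gives P = .028 at n = 66. The printed .04 fits n of 56 to 60.

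The rows checked seem to rest on different numbers of participants, with fewer in the DXA row. Step 1 therefore combines correlations that may come from different samples, and its results are illustrative.

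**The case against.** The case on the other side has real weight.

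- **The analysis is not wholly unadjusted.** A reader might infer that every planned association ignores other variables. The document does not support that. Lasso is multivariable, and thickness, area and perimeter, which are proxies for mass, are among the biomarkers. Covariate regression is also planned, and its covariate list may stand in an analysis plan not shown. What stands is narrower: the article never names muscle mass as something to condition on.
- **The primary objective is still answered.** The Abstract's Methods sets it as comparing performance, function, body composition and frailty or sarcopenia scales with biomarkers. Raw associations answer that, whether or not mass lies behind them. This is correct, and those correlations should stay. It does not cover the claim about muscle quality in the Introduction and the hypothesis in the Discussion.
- **Mass markers will not necessarily be mislabelled.** A reader might infer that the investigators will report a mass marker as a quality marker. That would be a prediction. The Results report the area and thickness correlations with DXA openly as such, and the Discussion calls morphological measures mass-linked. The document supports only that the stated analyses cannot separate the two.
- **The missing gold standard is disclosed.** True, and the study calls itself exploratory. Limitations does not, however, mention confounding with mass, and the clinical assessment it falls back on is the same set of reference variables.
- **The size is uncertain.** At an assumed grip-ALM correlation of 0.3, most of the area-grip correlation survives (0.26 of 0.372). Full explanation by mass needs about 0.69.
- **Strength per kg of lean mass is no reference standard.** Agreed. Grip is an upper-limb measure, while the scans are of the thigh, and the article describes quality through composition and microstructure.

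**Conclusion.** The point holds in a limited form. Muscle quality, as distinct from mass, is a stated target. No listed reference variable measures it, and no described analysis names mass as a conditioning variable. An association with grip, SPPB or gait speed therefore cannot be credited to quality rather than to lean mass.

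The size depends on a grip-ALM correlation that the document does not give. Over an assumed 0.3 to 0.7, the area-grip correlation falls from 0.372 to between 0.26 and -0.01. That range runs from modest shrinkage to complete loss, and it rests on Table 3 values whose sample is unclear. The structural point does not depend on those numbers.

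This is a change that should be made before analysis. It is not a flaw that undermines the frailty and function objective.

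**What to change.** 1. Keep the raw correlations as planned for the frailty and function objective.
2. Add to Statistical Analysis, for each biomarker and each combination model, the association with grip strength, SPPB and gait speed with DXA ALM and sex in the model. In the Lasso, enter ALM as an unpenalised term so that selection cannot drop it.
3. State in advance that a biomarker with no association beyond ALM will not be claimed as a marker of muscle quality. State also that an ALM-adjusted association supports, but does not prove, that a biomarker reflects quality.
4. Grip strength per kg of ALM may be reported as an exploratory descriptor only.

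**Cost.** Analysis wording and no new measurements, since DXA, grip, SPPB and gait speed are already planned in all three cohorts at both visits. The adjusted associations will tend to be smaller. Participants without DXA drop out of this analysis, and the sample sizes implied by Table 3 (about 56 to 60 for the DXA row checked, against 88 or more for the two non-DXA rows) suggest that this loss may not be negligible. The number with usable DXA should be reported beside the results.
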